#### Adverse outcomes

Any undesirable events occurring to a patient during the study will be considered an adverse outcome, whether or not to be considered concerning the experimental investigation.

### Statistical methods

#### Statistical analysis for primary and secondary outcomes

All statistical analyses will be performed by Stata 17 (Stata Corp, College Station, TX, USA), according to the intention-to-treat (ITT) approach. We will use multiple imputations based on chained equations, which fill in missing values in multiple variables iteratively using a sequence of univariate imputation models with a fully conditional specification of prediction equations. Baseline characteristics and clinical features will be described by mean ± SD and absolute frequency (percentages) and compared between two intervention groups using the independent sample t-test for continuous data and a chi-square test for categorical data. Before statistical comparisons, all data were checked visually by a normal quantile-quantile plot (Q-Q plot) in combination with the Kolmogorov-Smirnov test for additional verification. Linear mixed-effects models will be fitted to assess changes from baseline within the treatment groups and differences of those changes between the groups concerning continuous outcomes over time. The magnitude of the effect will be presented as an adjusted mean difference and its 95% confidence interval. Also, a log-binomial regression model using robust standard error will be used to evaluate the risk of categorical outcomes between two intervention groups. The magnitude of the effect will be presented as an adjusted risk ratio (RR) and its 95% confidence interval. The independent variables included in the model are the treatment group and all potential confounders. Significance is defined as *P* < 0.01.

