### Sample size

The sample size was calculated based on the primary outcome of the trial, the mRS. It was assumed that a total sample of 32 patients (32 patients per group), which includes a 10% dropout factor would provide 80% power to detect a difference in the mean of mRS between the royal jelly supplementation and placebo groups. Assuming means of 1.5 in the royal jelly supplementation group and 2.1 in the placebo group; a similar standard deviation (SD) of 0.8 between the two groups; and a two-sided test with a type I error of 0.05.

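### The planned change-from-baseline contrast does not match the quantity the trial was sized on; it has under 80% power if the baseline to 12-week correlation is below 0.5, and baseline adjustment is more efficient

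*Protocol article*

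**What the plan says.** In the Protocol article, Statistical analysis for primary and secondary outcomes, linear mixed-effects models are planned for "changes from baseline within the treatment groups and differences of those changes between the groups concerning continuous outcomes over time". The effect is to be reported as an adjusted mean difference. The covariates are described only as possible confounders alongside treatment group. The baseline value of the outcome is not named among them, and nothing says that the two arms share one baseline mean.

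The Sample size section works on a different quantity. It states "The sample size was calculated based on the primary outcome of the trial, the mRS", and claims 80% power with 32 patients per group, dropout of 10% allowed for. The stated aim of that power is "to detect a difference in the mean of mRS between the royal jelly supplementation and placebo groups". The effect is set by "Assuming means of 1.5 in the royal jelly supplementation group and 2.1 in the placebo group". The other inputs are a common SD of 0.8 and two-sided alpha 0.05. No SD of change and no correlation between visits is given.

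The Severity of stroke section schedules the mRS at two times only, baseline and post-intervention.

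**The concern.** The trial is sized on one quantity and analysed on another. A difference in means with SD 0.8 and a difference in mean changes have the same variance only at one particular correlation between visits. Below that correlation, the planned test of the primary outcome has less power than the Sample size section promises. Patients enter with acute stroke, and early disability may predict 12-week disability only weakly, so a low correlation is plausible. The article does not establish it.

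The choice of contrast also gives away precision. Baseline mRS is collected in every patient. Adjusting for it uses that information with the best weight, whereas subtracting it fixes the weight at 1 whatever the correlation. The same applies to the other continuous outcomes measured at baseline and 12 weeks.

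**Working it through.** **Inputs from the Sample size section.** Difference 2.1 − 1.5 = 0.6; SD 0.8 in each group; two-sided alpha 0.05; power 80%; 10% dropout; 32 per group. The text also calls 32 the total; 32 per group is the reading that reproduces.

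**Reproducing the stated figure.** The normal approximation gives 28 per arm (power 80.1%), and 28/0.9 = 31.1, rounded up to 32. The t-based calculation gives 29 per arm (power 80.1%), and 29 × 1.1 = 31.9, rounded up to 32. So 32 per group follows when 0.8 is the SD of the quantity compared. I use 29 evaluable per arm and the noncentral t distribution below.

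**What the planned contrast estimates.** In one simulated data set (29 per arm, SD 0.8 at both visits, true correlation 0.3):

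- Mixed model with group, time and group-by-time: −0.536, SE 0.208.
- Difference in mean change scores: −0.536, SE 0.208, the same.
- ANCOVA of the 12-week value on group and baseline: −0.483, SE 0.159.
- Change score with baseline as a covariate: −0.483, SE 0.159, the same as ANCOVA.
- Mixed model with a common baseline mean: −0.486, SE 0.170, close to ANCOVA.

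**Formulas.** Let ρ be the correlation between baseline and 12-week mRS, with SD 0.8 at both visits (an assumption; the article gives no baseline SD).

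- 12-week value: SD = 0.8
- Change: SD = 0.8 × √(2(1 − ρ))
- Baseline-adjusted: SD = 0.8 × √(1 − ρ²)
- Variance ratio, change to adjusted: 2(1 − ρ)/(1 − ρ²) = 2/(1 + ρ)

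Power comes from noncentrality 0.6/(SD × √(2/29)) on 56 degrees of freedom. For change at ρ = 0.3, SD = 0.8 × √1.4 = 0.947, noncentrality = 0.6/(0.947 × 0.2626) = 2.41, and power = 66%.

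| ρ | SD of change | Adjusted SD | Variance ratio | Power, 12-week value | Power, change | Power, adjusted |
|---|---|---|---|---|---|---|
| 0.2 | 1.012 | 0.784 | 1.67 | 80% | 60% | 82% |
| 0.3 | 0.947 | 0.763 | 1.54 | 80% | 66% | 84% |
| 0.5 | 0.800 | 0.693 | 1.33 | 80% | 80% | 90% |
| 0.7 | 0.620 | 0.571 | 1.18 | 80% | 95% | 98% |

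The adjusted column does not deduct the degree of freedom spent on the covariate; the effect is small.

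**Unequal SDs.** The variance of change is SD₀² + SD₁² − 2ρSD₀SD₁, with SD₀ at baseline and SD₁ at 12 weeks. It equals SD₁² when ρ = SD₀/(2SD₁). With SD₁ = 0.8, the break-even is 0.5/1.6 = 0.31 for a baseline SD of 0.5, and 1.1/1.6 = 0.69 for 1.1. The variance of change minus the adjusted variance SD₁²(1 − ρ²) is (SD₀ − ρSD₁)², which is never negative. With equal SDs it is positive for every ρ below 1.

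**The case against.** A reader might infer that the planned analysis simply loses power against the comparison used for sizing. The documents do not support that. With equal SDs the loss occurs only below a correlation of 0.5; above it the change contrast has more power than the sizing requires. Neither the correlation nor the baseline SD is given. Entry is limited to NIHSS 5 to 20, which may narrow the baseline spread and lower the break-even. This objection stands in full, and the loss must be stated as conditional.

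It can also be said that the plan may already be baseline-adjusted, since the effect is an adjusted one and the covariate list is open. This stands in part. A change score regressed on its own baseline is ANCOVA, and a mixed model with a common baseline mean would also fit the quoted sentence. But in a mixed model where baseline is already one of the outcome rows, a covariate entered as a main effect does not alter the group-by-time estimate. In simulated data at ρ = 0.3 that estimate was −0.499 with no covariate, with a severity covariate and with baseline mRS itself; the change-score SE was 0.274, against 0.220 for ANCOVA. An open list of confounders therefore does not by itself turn the stated contrast into ANCOVA.

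Two premises are inferred. The article does not list mRS among the continuous outcomes, nor say that the means of 1.5 and 2.1 are 12-week values. Sizing on means supports the first; the lower mean in the active arm fits final scores and supports the second.

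Two further readings go too far. Nothing in the article says that within-arm changes will be presented as evidence of efficacy. And the line "Significance is defined as *P* < 0.01" conflicts with the sizing alpha, but that is a separate matter, so every power figure here uses 0.05.

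Finally, the mRS is an ordinal 0 to 6 scale that includes death. Baseline adjustment keeps the linear model for means already implied by the plan; it does not resolve that question.

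**Conclusion.** The point holds in conditional form. The article fixes a contrast, differences in change from baseline, that is not the quantity behind its sample size. With SD 0.8 at both visits, separate baseline means per arm, 29 evaluable per arm and alpha 0.05, the power of that contrast ranges from 60% to 95% as the correlation goes from 0.2 to 0.7, crossing the stated 80% at 0.5. The crossing moves if the baseline SD differs from 0.8. Whether power is actually lost against the sizing cannot be settled from the article.

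The comparison with baseline adjustment does not depend on that. With equal SDs, the change contrast has 1.67 to 1.18 times the variance of the adjusted one over the same range, and it is less efficient at every correlation below 1. Adjusted analysis keeps power at about the sized 80% or above whatever the correlation. This is an improvement worth making, not a flaw that invalidates the trial.

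**What to change.** State that the primary estimate is the between-group difference in 12-week mRS adjusted for baseline mRS, optionally also for baseline NIHSS. Fit it by ANCOVA, or by a mixed model constrained to one baseline mean for both arms, which is nearly equivalent. Use the same form, each with its own baseline value, for every other continuous outcome measured at baseline and 12 weeks. Report within-arm change descriptively, without P values.

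This changes the model statement only. It needs no further patients or measurements, because baseline mRS and NIHSS are already collected, and it spends one or two degrees of freedom. Make the change before unblinding.

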### Outcomes

#### Severity of stroke

The severity of ischemic stroke will be evaluated by a neurologist ([name]) at baseline and post-intervention using a modified Rankin Scale (mRS). It evaluates the degree of disability or dependence in the daily activities of individuals with stroke as follows: 0 (no symptoms), 1 (no significant disability; able to carry out all usual activities, despite some symptoms), 2 (slight disability; able to look after own affairs without assistance, but unable to carry out all previous activities), 3 (moderate disability; requires some help, but able to walk unassisted), 4 (moderate to severe disability; unable to attend to own bodily needs without assistance, and unable to walk unassisted), 5 (severe disability; requires constant nursing care and attention, bedridden, incontinent), and 6 (dead) [25].

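### The likely primary analysis of the mRS is a linear model that scores death as one more equal step; an ordinal analysis with deaths kept at 6 should be named instead

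*Protocol article*

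**What the plan says.** **Primary outcome and sizing** (Sample size): "The sample size was calculated based on the primary outcome of the trial, the mRS". The planning values are means with a common SD of 0.8: "Assuming means of 1.5 in the royal jelly supplementation group and 2.1 in the placebo group". The test is two-sided at 0.05 with 80% power, and 32 per group includes a 10% dropout allowance.

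**The scale** (Severity of stroke): the mRS is taken "at baseline and post-intervention using a modified Rankin Scale (mRS". It has seven ordered grades, starting at "0 (no symptoms), 1 (no significant disability; able to carry out all usual activities, despite some symptoms" and ending at "5 (severe disability; requires constant nursing care and attention, bedridden, incontinent), and 6 (dead".

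**The models** (Statistical analysis for primary and secondary outcomes): linear mixed-effects models cover changes within groups and "differences of those changes between the groups concerning continuous outcomes over time", reported as an adjusted mean difference. For the other outcomes, "a log-binomial regression model using robust standard error will be used to evaluate the risk of categorical outcomes between two intervention groups", reported as a risk ratio. The section does not say which model takes the mRS, and the article gives no ordinal method and no mRS cut-point.

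**Deaths:** Eligibility criteria lists death during the study among the exclusions. The analysis section says all analyses run "according to the intention-to-treat (ITT) approach", with multiple imputation of missing values.

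**The concern.** The two named models do not suit the scale equally badly. A log-binomial model takes a two-level response. It cannot be fitted to seven mRS grades, nor to the bands given for the MMSE (four), each DASS-21 domain (five) or the FSS (three). The SNAQ threshold of 14 is the one evident two-level split. For the mRS that leaves the linear model, which treats the step from 5 to death as equal to the step from 0 to 1. Because the planning means lie near 2, a death sits about four units away from the rest of the data, and a few deaths can dominate the variance.

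At stake is the power of the primary comparison, together with a gap in the plan: a patient who dies could be dropped under the exclusion list, imputed as missing, or scored 6.

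**Working it through.** **1. The plan's own figure.** Inputs from Sample size: δ = 2.1 − 1.5 = 0.6, SD 0.8, two-sided 0.05, 80% power.

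n per arm = 2 × (1.960 + 0.842)² × 0.8² / 0.6² = 27.9, so 28. With 10% dropout, 28 / 0.9 = 31.1, so 32.

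The stated 32 reproduces as a per-group figure. It rests on a two-sample comparison of means, so the mRS was treated as continuous when the trial was sized.

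**2. What deaths do to the SD.** Suppose a fraction d of each arm scores 6, and survivors have mean m and SD 0.8.

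Variance = (1 − d) × 0.64 + d(1 − d)(6 − m)². Difference in means = (1 − d) × 0.6.

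For d = 0.05:
- royal jelly: 0.608 + 0.0475 × 4.5² = 1.570, SD 1.25
- placebo: 0.608 + 0.0475 × 3.9² = 1.331, SD 1.15
- difference 0.57, average variance 1.450, pooled SD 1.20

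Power at 32 per arm ≈ Φ(0.57 / 1.204 × √16 − 1.96) = Φ(−0.07) = 47%.

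The same formula gives 85% at d = 0, 66% at d = 0.02 (difference 0.588, pooled SD 0.987) and 31% at d = 0.10 (difference 0.54, pooled SD 1.474).

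**3. Linear against rank analysis, by simulation.** Survivors were drawn from a rounded normal on 0 to 5, with mean and SD matched exactly to 1.5 or 2.1 and 0.8. The death fraction was added at 6, with 32 per arm and two-sided 0.05. The t-test stands in for the linear model and the Wilcoxon rank-sum test for an unadjusted proportional-odds model. Ranges show repeat runs.

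| Deaths per arm (assumed) | t-test | Rank test |
|---|---|---|
| 0% | 84–85% | 83% |
| 2% | 66% | 78% |
| 5% | 48–49% | 72% |
| 10% | 32% | 61–62% |

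With no true difference, both tests rejected in about 5% of runs at every death rate tried.

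**4. Could the planned SD of 0.8 already include deaths?** If M is the mean over all patients, deaths alone contribute d(6 − M)²/(1 − d) to the variance. Setting this equal to 0.64 gives d/(1 − d) = 0.64/20.25 for M = 1.5 and 0.64/15.21 for M = 2.1, so d = 3.1% and 4.0%. Above those rates an SD of 0.8 is impossible, even if every survivor had the same score. One death in 32 is already 3.1%.

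**The case against.** A reader might infer that the plan has no usable primary analysis, or that the primary test could be a mean difference or any split of the mRS chosen after the data are seen. The article does not support that. The sample size is for a difference in means and the analysis section reports an adjusted mean difference, so together they point to the linear model. No dichotomised mRS is proposed anywhere, so the power of such a split is not a cost of this plan. Nor is the linear model invalid: its type I error holds, and without deaths it is 1 to 2 points better than the rank test. The bands for the secondary scales are given for interpretation and are not assigned to the log-binomial model. Totals may well be what is meant.

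It is also fair to say that the case rests on deaths, that the article gives no death rate, and that its exclusion list might keep every 6 out of the data. The last point does not clear the plan. Removing patients who die after randomisation contradicts the intention-to-treat statement, and imputing an mRS for them would discard an outcome that the scale itself defines.

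Three technical limits stand. The simulation has no baseline or covariates, whereas the plan's model is longitudinal and adjusted. Equal death rates with a shift among survivors are not exactly proportional odds, so a common odds ratio would then be an average. All the figures use 0.05 from Sample size, whereas the analysis section sets P < 0.01. At 0.01, 5% deaths and 32 per arm, power is about 27% (t-test) against 47% (rank test).

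**Conclusion.** The point holds as a recommendation to change the method, not as a finding that the primary test is invalid. The linear model is the likely but unassigned analysis of a seven-level ordinal scale ending in death, and the log-binomial model cannot take that scale. If nobody dies, the choice hardly matters. If deaths score 6, the linear analysis falls behind by about 12 points of power at 2% deaths, 23 to 24 at 5% and 29 to 30 at 10%. These sizes assume survivors at the planning means and SD, equal death rates in the arms, 32 analysed per arm and two-sided 0.05. The death rates are illustrative. Independently of them, the article does not settle whether a 6 enters the analysis.

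**What to change.** Before unblinding, state the primary analysis in words such as these: mRS at week 12 on the full 0 to 6 scale, with deaths kept as 6 and neither excluded nor imputed, analysed by a proportional-odds model with treatment, baseline mRS, baseline NIHSS and age, and reported as a common odds ratio with its confidence interval; the mean difference is supportive.

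Reconcile the listing of death under the exclusion criteria with the intention-to-treat statement, for the purposes of the analysis. Restrict risk ratios to outcomes with two levels, such as the SNAQ threshold, and say that the MMSE, DASS-21 and FSS are analysed as scores.

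The cost is about 1 to 2 points of power if nobody dies, and a headline effect that is no longer a mean difference. The stated 80% power was derived for means, so it must be rechecked for the ordinal analysis. No new data are needed. The article reports recruitment still in progress, with 43 patients included on 15 August 2022; whether the blind has since been broken cannot be told from it.

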### Objectives

We will aim to investigate the effects of royal jelly supplementation on oxidative stress, inflammatory mediators, mental health, cognitive function, quality of life, stroke severity, appetite, and fatigue of patients with ischemic stroke.

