## Discussion

There is growing evidence on complementary and alternative medicine use among those with chronic disease. Patients tend to go for alternative approaches to boost the immune system and cure side effects owing to the chronic nature of the diseases [39, 40]. According to various reports, over 50% of patients with stroke reported using complementary and alternative medicine [41–43]. Therefore, due to global interest in using these alternative therapies, more evidence is required to assess their efficacy and safety.

The current study is designed to investigate the efficacy and safety of royal jelly supplementation in a randomized, parallel, two-arms, single-center, triple-blind, placebo-controlled manner. This study will provide evidence as a phase III clinical trial.

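### One P < 0.01 rule covers the mRS and about 25 other outcomes, leaves secondary results without a stated role, and conflicts with the 0.05 used for sizing

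*Protocol article*

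**What the plan says.** The protocol article identifies its primary outcome in *Sample size*: "The sample size was calculated based on the primary outcome of the trial, the mRS". That section assumes mean scores of 1.5 on royal jelly and 2.1 on placebo, and an SD of 0.8 in each arm. It sets the level as "a two-sided test with a type I error of 0.05". The planned number "would provide 80% power to detect a difference in the mean of mRS".

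*Objectives* names eight effect areas in one list without ranking them: "oxidative stress, inflammatory mediators, mental health, cognitive function, quality of life, stroke severity, appetite, and fatigue of patients with ischemic stroke".

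*Statistical analysis for primary and secondary outcomes* describes the models and ends with one threshold for everything: "Significance is defined as" P < 0.01. It reports effects with 95% confidence intervals. It gives no separate level for the mRS, no testing order, no multiplicity adjustment and no exploratory label.

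*Discussion* states the trial's standing: "This study will provide evidence as a phase III clinical trial".

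**The concern.** There are two problems in one sentence.

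First, the article lays down a decision rule that treats the mRS and every other outcome alike, and nothing elsewhere limits what a secondary result may support. The trial could be null on the one outcome it was sized for and still report a significant effect of royal jelly from one marker or questionnaire. With this many outcomes, chance alone would produce such a result more often than a reader would expect from a 1% threshold.

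Second, the level is not the one used for the sample size. If the mRS is judged at 0.01, the stated 80% power does not apply to the test that will be run.

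**Working it through.** **1. The plan's own sample size.** Inputs from *Sample size*: difference 2.1 − 1.5 = 0.6, SD 0.8, two-sided alpha 0.05, power 80%, dropout 10%.

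n per group = 2 × [0.8 × (1.960 + 0.842) / 0.6]² = 27.9, so 28. With dropout, 28 / 0.9 = 31.1, so 32.

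The planned 32 per group is reproduced, and it rests on alpha 0.05. (A t-test version gives 29, then 33.)

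**2. Power for the mRS at the stated threshold.** Power = Φ(0.6 / [0.8 × √(2/n)] − c), with c = 1.960 at 0.05 and 2.576 at 0.01.

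| Per group | At 0.05 | At 0.01 |
|---|---|---|
| 28 completers | Φ(2.806 − 1.960) = 80% | Φ(2.806 − 2.576) = 59% |
| 32, no dropout | Φ(3.000 − 1.960) = 85% | Φ(3.000 − 2.576) = 66% |

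By t-test, the 0.01 figures are 56% and 63%. Keeping 80% power at 0.01 needs 2 × [0.8 × (2.576 + 0.842) / 0.6]² = 41.5, so 42 per group, or 42 / 0.9 = 46.7, so 47 with dropout.

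**3. Counting the other outcomes.** From the subsections under *Outcomes*:

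- MMSE 1, DASS-21 domains 3, FSS 1, SNAQ 1, SS-QOL total 1
- blood pressure 2 (assumed systolic and diastolic), MUAC 1
- laboratory 15: TAC, TOS, MDA, NO, SOD, GPx, CRP, ESR, BDNF, TC, TG, LDL-C, HDL-C, FPG, UA

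The total is 1 + 3 + 1 + 1 + 1 + 2 + 1 + 15 = 25, leaving out dietary intake. Other defensible counts:

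- 24, if blood pressure counts once.
- 15, if limited to areas named in *Objectives*: six oxidative markers, two inflammatory, three DASS-21 domains, MMSE, SS-QOL, SNAQ and FSS.
- 25 + 12 = 37, with the SS-QOL sub-classes added.

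**4. Chance of at least one false-positive secondary result.** All m outcomes are taken as truly null and each is tested two-sided at 0.01. The documents give no correlations, so a common correlation ρ is assumed, from 0 to 0.8.

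- Independent, either direction: 1 − 0.99^25 = 22.2%.
- Independent, benefit only (0.005 per outcome): 1 − 0.995^25 = 11.8%.
- Correlated, either direction: 1 − ∫ φ(z) [Φ((c − √ρ z)/√(1−ρ)) − Φ((−c − √ρ z)/√(1−ρ))]^m dz, with c = 2.576. For benefit only, drop the second Φ term.

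| m | Direction | ρ = 0 | ρ = 0.5 | ρ = 0.8 |
|---|---|---|---|---|
| 25 | either | 22.2% | 13.7% | 6.6% |
| 25 | benefit | 11.8% | 6.9% | 3.3% |
| 15 | either | 14.0% | 9.7% | 5.3% |
| 15 | benefit | 7.2% | 4.9% | 2.6% |
| 37 | either | 31.1% | 17.4% | 7.8% |
| 37 | benefit | 16.9% | 8.7% | 3.9% |

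A simulation of one million draws at m = 25 agrees with the formula.

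**The case against.** The strongest reply is that a condensed article commonly leaves multiplicity rules for secondary outcomes to an analysis plan, which is not shown here. That is fair as far as the absence of an adjustment goes. But the article is not silent: it fixes a significance rule and applies it to primary and secondary outcomes together. The clash between 0.01 and 0.05 is also on the page and needs no other document.

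The threshold is also stricter than usual. At 0.05, 25 independent outcomes would give 1 − 0.95^25 = 72% in either direction, against 22% at 0.01. This stands and keeps the size of the problem moderate. The article does not present 0.01 as multiplicity protection, however, and the price is paid by the one outcome that was sized.

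Three stronger readings are tempting and should be set aside.

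- A reader might take 14% as the chance of a false benefit. It counts differences in both directions; the figure for benefit is about half.
- A reader might say there is no hierarchy. The mRS is named as the single primary outcome, and the order of topics in *Objectives* is not a testing order. What is missing is a stated role for the other outcomes.
- A reader might say the plan treats a secondary P < 0.01 as confirmed efficacy. No sentence says so, and *Dissemination plans* commits to reporting both negative and positive findings. The plan permits that claim by not ruling it out.

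The count of 25 is a judgement. With about 15 outcomes the chance of a false benefit is about 5%, and the concern is correspondingly smaller.

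**Conclusion.** The concern holds in this form. One threshold of P < 0.01 covers the primary and about 25 other outcomes, and the secondary results have no stated role. Under no effect, the chance of at least one significant secondary difference is about 14% (7% to 22%), and of at least one significant benefit about 7% (3% to 12%). These figures rest on 25 outcomes, all truly null, with an assumed common correlation of 0.5 (range 0.8 to 0).

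The conflict over the primary level is firmer, because it uses only the plan's own inputs: the design gives 80% power at 0.05 but about 59% at 0.01 with 28 completers per group. Both matters should be settled before unblinding. Neither undermines the choice of a single primary outcome.

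**What to change.** In *Statistical analysis for primary and secondary outcomes*, replace the significance sentence with:

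> The between-group comparison of mRS at 12 weeks is the only confirmatory test, two-sided at alpha 0.05 as used for the sample size. All other outcomes are secondary/exploratory, reported as estimates with 95% confidence intervals without multiplicity adjustment, and no claim of efficacy will be based on them.

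If 0.01 is kept for the mRS instead, restate the power in *Sample size* as about 59%.

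If confirmatory secondary claims are wanted, name a short list now (for example SS-QOL total, MMSE and FSS) and test it by Holm at 0.05, only if the mRS test is positive. In *Objectives*, put stroke severity by mRS first and label the rest secondary/exploratory.

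This is a change of wording, with no extra patients, visits or data. The cost is that an isolated biomarker or questionnaire finding can no longer be called a confirmed effect. The primary level does change relative to the current analysis section, from 0.01 to 0.05, which restores the planned 80% power. The change should be dated and made before unblinding.

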### Randomization

Randomization numbers will be provided by an independent statistician using permuted block randomization approach. Eligible patients will be randomly allocated to the intervention or the control groups in a ratio of 1:1 using computer-generated random numbers [STATA software, version 16 (Stata Corp, College Station, TX, USA] and block size six.

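### The trial is sized for a two-sided 0.05 test, but the analysis section requires P < 0.01; on the plan's own assumptions the 80% power for mRS then falls to about 58%

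*Protocol article*

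**What the plan says.** The Sample size section names mRS as the primary outcome and sizes the trial on its mean. It expects a mean of 1.5 with royal jelly against 2.1 with placebo, takes a common SD of 0.8, and specifies "a two-sided test with a type I error of 0.05". The target is 32 in each arm, to give 80% power after allowing for 10% dropout. Allocation is 1:1 (Randomization section).

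The section headed Statistical analysis for primary and secondary outcomes ends with a single rule: "Significance is defined as *P* < 0.01". It does not exempt the primary outcome or give a reason for the stricter level. For continuous outcomes the same section says "The magnitude of the effect will be presented as an adjusted mean difference and its 95% confidence interval", and it uses 95% intervals for risk ratios too. The article plans no interim analyses, so sharing alpha across looks cannot explain the 0.01.

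**The concern.** The article gives two incompatible rules for its main result: one that the sample size was built on, and a stricter one that the analysis will apply. Two things are at stake.

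- **Power.** If the analysis section is followed, the trial's chance of a positive primary result is well below the stated 80%, under the assumptions the plan itself makes.
- **Interpretation.** A primary result with P between 0.01 and 0.05 would have a 95% interval that excludes no effect, yet be declared non-significant. With 0.05 and 0.01 both in the published text, either conclusion could be defended after the data are seen, which is what a pre-specified threshold is meant to prevent.

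**Working it through.** **Inputs, all from the Sample size section.** Means 1.5 and 2.1, so the difference is 0.6; SD 0.8 in both groups; standardised difference d = 0.6/0.8 = 0.75; 80% power; two-sided 0.05; 10% dropout; 32 per group. The text also calls 32 the total ("a total sample of 32 patients (32 patients per group"), but only the per-group reading reproduces, and the Trial status section already reports 43 patients included. The 0.01 comes from the analysis section. It does not restate sidedness, so I take it as two-sided.

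**Step 1: reproduce the plan's figure at 0.05.** By the normal approximation,

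n per group = 2 × (z(1−α/2) + z(0.80))² / d² = 2 × (1.960 + 0.842)² / 0.75² = 27.9, so 28.

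Dividing by 0.9 for dropout gives 31.1, so 32 per group, which matches the protocol. The exact t-test version needs 29 analysed per group, which becomes 33 (29/0.9) or 32 (29 × 1.1). The sample size arithmetic is sound for 0.05.

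**Step 2: change only alpha.** The number analysed after dropout is 32 × 0.9 = 28.8, about 29 per group. Power by the normal approximation is Φ(d√(n/2) − z(1−α/2)). At n = 29, d√(n/2) = 0.75 × √14.5 = 2.856, so:

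- α = 0.05: Φ(2.856 − 1.960) = 81.5%
- α = 0.01: Φ(2.856 − 2.576) = 61.0%

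The exact (noncentral t) calculation gives slightly lower values:

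| Analysed per group | t-test, α 0.05 | t-test, α 0.01 | Normal approx., α 0.05 | Normal approx., α 0.01 |
|---|---|---|---|---|
| 28 | 78.7% | 55.7% | 80.1% | 59.1% |
| 29 | 80.1% | 57.7% | 81.5% | 61.0% |
| 32 (no loss) | 84.0% | 63.4% | 85.1% | 66.4% |

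**Step 3: what 0.01 would require.** With 29 per group, the difference detectable with 80% power rises from 0.60 to 0.74 mRS points. For 80% power at a difference of 0.6, the t-test needs 44 analysed per group, and 44/0.9 = 48.9, so 49 randomised. The normal approximation gives 42 and 47. The plan has 32.

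**Step 4: how often the two rules would disagree.** At 29 per group the two power figures differ by 80.1% − 57.7% = 22.4%. If the assumed effect is real, about 22% of such trials would end with P between 0.01 and 0.05.

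**Step 5: does 0.01 serve as a multiplicity rule?** The Outcomes section lists about 25 secondary measures: MMSE, three DASS-21 domains, FSS, SNAQ, SS-QOL, two blood pressures, MUAC and 15 blood markers. At 0.01 each, the chance of at least one false positive is 1 − 0.99²⁵ = 22% if they were independent. They are correlated, so this is only a guide. Applying 0.01 to the single primary test does nothing to reduce it.

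**The case against.** **The 0.01 may be a misprint.** The sample size and both references to 95% intervals point to 0.05, and one sentence stands alone. If so, the 80% power stands. The decision rule as published is still wrong and needs the same correction.

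**The 58% is not the power of the planned analysis.** This is fair. The plan uses intention-to-treat with multiple imputation and an adjusted mixed model for change from baseline, and power then depends on the correlation between baseline and 12-week mRS, which the article does not give. For assumed correlations of 0.3, 0.5 and 0.7, with 29 per group and α = 0.01, t-test power is about 63%, 73% and 90% for a baseline-adjusted comparison, and 41%, 58% and 84% for simple change scores. Adjustment could therefore recover the loss only if the correlation is high. The stated 80% does not rely on any such gain, so the like-for-like comparison is 80% against 58%.

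**A 95% interval beside a stricter threshold is not an error in itself.** That is true where the rule is deliberate and explained. Here it corroborates the inconsistency and is not a second defect.

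**Multiplicity is a side issue.** The article never claims that 0.01 controls error over the secondary outcomes, and that handling may be left to the SAP. I accept this. The point shows only that multiplicity gives no ready justification for using 0.01 on the primary outcome.

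**An unseen SAP may settle it.** An SAP could choose one level, but the article states both and they conflict. This is a contradiction in the text, not an omission.

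**Conclusion.** The concern holds. The article fixes two different significance levels for its primary outcome and does not reconcile them. If the analysis section is followed, the stated 80% power becomes about 58% with 29 analysed per group. The range is 56% to 63% for 28 to 32 per group by t-test, and 66% at most by the normal approximation with no losses. These figures rest on the Sample size section's own difference and SD, and on an unadjusted two-sided two-sample comparison; the gain or loss from the planned baseline modelling cannot be determined from the article. If 0.01 was a slip, the power is right and the decision rule is wrong. Either way, the criterion for primary success must be corrected before unblinding.

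**What to change.** Fix one level for the primary outcome and match the power and the interval to it.

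- **Preferred:** state that 12-week mRS is the single primary test, at two-sided 0.05, reported with a 95% confidence interval. This is the level the sample size already specifies. Confine P < 0.01 to the secondary outcomes, labelled supportive and shown with 99% intervals. If formal error control over them is wanted, use a Holm adjustment, because 0.01 per test does not provide it.
- **If the sponsor means 0.01 for the primary:** restate the power as about 58% (detectable difference 0.74 mRS points at 80% power with 29 per group) and report 99% intervals.

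The cost is one sentence in the analysis section and no extra patients. Because recruitment was under way and 0.01 is already published, the change should be a dated amendment made before unblinding, citing the 0.05 in the Sample size section as its basis. Keeping 0.01 costs only a less favourable power statement.
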